### 2.7 Intervention

#### Group-based exercise

The group-based exercise (GBE) programme will be delivered by two physical therapists (experience in musculoskeletal rehabilitation in primary health care). The GBE comprises three sessions per week of group-based exercise in a local community center, for 8 weeks [44]. Each group session will consist of 10 to 18 participants and each exercise session will last 60 minutes and consist of four stages: (1) five minutes warm up (i.e., self-regulated walk); (2) twenty minutes of moderate intensity walking; (3) thirty minutes of resistance training for the major muscles of the leg, trunk and arm and balance exercises that progress in difficulty; and (4) five-minute cool down period (i.e., self-regulated walk). The exercise intensity will be assessed by one of the following criteria: (1) point of volitional fatigue [45] for the resistance training component; and (2) perceived effort ranging from 3 to 4 on the modified 10-point Borg scale score for the walking component [45]. The intensity will be increased along the 8-week programme following the recommendations of the ACSM guideline [32] (i.e., resistance exercise- a gradual progression of more repetitions per set; and aerobic exercise- a gradual progression of exercise volume by adjusting exercise intensity) [32].

The GBE programme was set up based on tasks that makes part of performance-based assessment instruments widely used for the evaluation of physical performance of the older people (i.e., Berg Balance Scale [46], Dynamic Gait Index [47] and Timed Up and Go [48]). In addition, exercises commonly used in primary health care groups were added [49–51]. The protocol will take place in a gymnasium and will be supervised by a trained physical therapist [52–54]. Examples of the choices of exercises are provided in the S1 Appendix.

Modifications were performed after registration of the clinical trial. We included 5 minutes of warm-up and 5 minutes of cool-down during the intervention. To reduce the risk of injury during the protocol. Furthermore, based on recommendations of the ACSM guideline, criteria were established to intensity increase along the 8-week. All these changes were made before starting to recruit participants. Furthermore, the registry has been updated and is available with new information.

#### Control group

Participants randomly allocated to control group will remain on a waiting list. In addition, weekly contact will be made to ensure that they do not start treatment during the study protocol. However, previous treatments like medications will be allowed.

### 2.8 Data analysis

#### Sample size calculation

The sample size calculation was performed using the G*Power 3.1 software. The difference between means of a meta-analysis 1.7 [26] was divided by the standard deviation of the study of Zadro (2019) [55] 4.80 to obtain Cohen’s d. Considering the Cohen’s d, a sample size of 120 participants was calculated (60 in each group), with a statistical power of 80%, alpha of 5%, and 20% dropout rate.

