#### Analysis of treatment effects

The statistical analysis will be performed following the intention-to-treat analysis principles [56, 57]. The blinded statistician will be given coded data, the normality will be tested using the Kolmogorov-Smirnov test and the homoscedasticity of the data will be tested using the Levene test. Then, considering normal distribution, an analysis of mixed linear models (random intercepts and fixed coefficients) will be conducted, which incorporated terms for treatment, time, and the treatment-time interactions. As two physical therapists will be responsible for implementing the GBE will be applied multilevel analyses with participants nested by physiotherapist. In this sense, level 1 being the different time points, level 2 the subject, and level 3 the physical therapists.

Mean differences and their confidence intervals (CIs) at 95% will be presented. Primary outcome results will be interpreted based on the minimal clinically important difference (MCID) estimated for the adult population (i.e., RMDQ > 5 and NRS > 2) points [58]. All statistical analyses will be performed with SPSS (IBM Corp. Released 2013. IBM SPSS Statistics for Windows, Version 22.0. Armonk, NY: IBM Corp).

In addition, the sample will be dichotomized for improvement / maintenance according to the clinically important differences. The absolute risk reduction will be obtained by subtracting the GBE group risk by the control group risk. This data will be used to calculate the number needed to treat (NNT) (100% / by reducing the absolute risk).

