### 3.2 Study strengths and weaknesses

The main strength of this study protocol is that it is a randomized controlled trial with concealed allocations. The sample size was calculated to provide adequate statistical power to detect intergroup differences in the primary outcome. The physio therapist responsible for supervising the strengthening protocol will have similar clinical experience and will receive prior training.

The main limitation of our study is that the participants and therapists will not be blinded to the group allocations. In addition, it is not possible to affirm the blinding of the evaluator due to the fact that our outcomes are reported by patients, so the patient is his own evaluator.

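### The stated 80% power assumes independent participants, although exercise is delivered in groups by two therapists and the planned model nests participants by therapist

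*Protocol article*

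**What the plan says.** The Sample size calculation in section 2.8 builds a standardised effect from two outside figures: "The difference between means of a meta-analysis 1.7 [26] was divided by the standard deviation" of a second cited study, "4.80 to obtain Cohen’s d". It then reports: "Considering the Cohen’s d, a sample size of 120 participants was calculated (60 in each group), with a statistical power of 80" per cent, with 5% alpha and 20% dropout, from G*Power. Those are all the inputs named.

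Three other places bear on whether participants can be treated as independent:

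- Section 2.7, Group-based exercise: two physical therapists deliver the programme, and "Each group session will consist of 10 to 18 participants".
- Section 2.7, Control group: controls stay on a waiting list, with weekly contact but no grouped treatment.
- Section 2.8, Analysis of treatment effects: because two therapists deliver the programme, there "will be applied multilevel analyses with participants nested by physiotherapist". Time points are level 1, participants level 2 and therapists level 3.

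Section 3.2 then lists the sizing as a strength: "The sample size was calculated to provide adequate statistical power to detect intergroup differences in the primary outcome".

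**The concern.** The sizing and the analysis sit in the same section and make different assumptions. A calculation from Cohen's d, alpha, power and dropout alone describes two samples of unrelated individuals. The analysis paragraph expects outcomes to be correlated among participants treated by the same therapist, and group delivery is a second possible source of correlation. Both sources exist in the exercise arm only.

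Positive correlation in that arm inflates the variance of its mean, and so the standard error of a between-arm difference at follow-up. The 80% would then be too favourable for that contrast. Correcting only the arithmetic behind 120 would carry the same independence assumption into the new figure. The adequate-power statement in section 3.2 rests on it too, and a null result for pain or disability could be read as more informative than it is.

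**Working it through.** **Inputs from the Protocol article.** Difference 1.7 and SD 4.80, so d = 1.7/4.80 = 0.354 (the scale of these figures is not stated); 60 per arm; 20% dropout, so 60 × 0.8 = 48 analysed per arm; alpha 5% (sidedness not stated; two-sided used below); exercise groups of 10 to 18; two therapists.

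**Assumptions.** ICC of 0.01 to 0.10, because the documents give none. Analysed cluster size m: by exercise group, 10 × 0.8 = 8 to 18 × 0.8 = 14.4, taking group membership as fixed; by therapist, 48/2 = 24, taking an even split.

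**Step 1: the plan's own figure.** A two-sample t-test with d = 0.354 and 80% power needs 127 per arm two-sided, 254 in total, and 254/0.8 = 318 with dropout. One-sided it needs 100 per arm, 200 in total, and 250 with dropout. The stated 120 is not reproduced. With 48 per arm, two-sided power at d = 0.354 is 40.4%. This is a separate error. To isolate the effect of clustering, a second benchmark is used: the effect that 48 per arm detects with exactly 80% power under independence, d = 0.578, or 0.578 × 4.80 = 2.77 points.

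**Step 2: clustering in one arm.** With DE = 1 + (m − 1) × ICC in the exercise arm and none in the control arm, the variance of the difference is multiplied by (1 + DE)/2. The noncentrality d × √(48/2) is divided by the square root of that factor. Degrees of freedom stay at 2 × 48 − 2 = 94, which is generous.

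*Worked case, therapist level, ICC 0.05.* DE = 1 + 23 × 0.05 = 2.15. The variance factor is (1 + 2.15)/2 = 1.575, with square root 1.255. Noncentrality is 0.578 × 4.899 = 2.83, and 2.83/1.255 = 2.26. Power is 60.7%.

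**Power at d = 0.578 (80% under independence):**

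| ICC | m = 8 | m = 14.4 | m = 24 (therapist) |
|---|---|---|---|
| 0.01 | 78.6% | 77.4% | 75.6% |
| 0.02 | 77.3% | 74.9% | 71.4% |
| 0.05 | 73.4% | 67.9% | 60.7% |
| 0.10 | 67.4% | 58.2% | 48.0% |

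A loss of 5 points or more therefore starts at an ICC of about 0.02 to 0.05 by exercise group, depending on its size, and between 0.01 and 0.02 by therapist.

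**Power at the plan's d = 0.354, ICC 0.05:** 40.4% falls to 35.4% (m = 8), 31.8% (m = 14.4) or about 28% (m = 24).

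**Difference detectable with 80% power, ICC 0.05:** 2.77 points times the square root of the variance factor. This gives 2.77 × 1.084 = 3.0 (m = 8), 2.77 × 1.155 = 3.2 (m = 14.4) and 2.77 × 1.255 = 3.5 (m = 24).

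**Step 3: does the contrast matter?** Take unit outcome variance, correlation 0.5 between time points, 48 per arm and two therapists in the exercise arm. A therapist effect with variance 0.05 that is constant over time adds 0.05/2 = 0.025 to the variance of the between-arm difference at one time: 2/48 = 0.0417 becomes 0.0667. For the treatment-by-time contrast (change from baseline compared between arms) the same effect cancels, and the variance stays at 0.0417.

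**The case against.** The strongest reply is that the loss is not shown for the analysis as written. The model has random intercepts and treatment-by-time terms, and outcomes are measured at baseline and three later times. If the primary contrast is the interaction, Step 3 shows that a constant therapist intercept drops out. This stands in part. The Protocol article says only that mean differences will be presented, so the contrast is open. Correlation that arises only after treatment starts would not cancel, but the written model has no term for it.

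Second, baseline adjustment could recover power. With an assumed baseline correlation of 0.5 (not in the documents), the residual variance falls by the factor 1 − 0.5² = 0.75. Power at d = 0.578 and ICC 0.05 is then about 80–85% by exercise group and 73% by therapist. This also stands, although the sample-size paragraph claims no such gain.

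A reader might therefore infer too much by concluding that the planned analysis certainly falls short of its stated power. The documents do not support that: they fix neither the contrast nor any baseline correlation.

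Third, the size rests on an assumed ICC, and at 0.01 by exercise group the loss is only 1 to 3 points. That is correct, and it is why a range is shown. The written model also has a therapist level and no exercise-group level, so the group figures are a sensitivity analysis. Fixed group membership is itself an assumption.

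Fourth, results will be read from 95% confidence intervals against thresholds of more than 5 points for disability and more than 2 for pain. This limits the harm from an optimistic planned power but does not make the stated figure right.

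Finally, a journal article condenses its source. Here, however, the article states both its sizing inputs and its clustered analysis, and calls the power adequate. The point is a mismatch between statements, not a missing detail.

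**Conclusion.** The mismatch is real: the 80% was derived as if participants were independent, and the plan's own analysis does not treat them so. For a between-arm difference at a follow-up time, with no baseline or repeated-measures gain, any positive ICC in the exercise arm puts power below the independent-data figure.

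The size depends on an ICC that the documents do not give. From an 80% starting point, power at ICC 0.01, 0.05 and 0.10 is about 77–79%, 68–73% and 58–67% by exercise group, and 76%, 61% and 48% by therapist. With only two therapists or a handful of groups, the few effective degrees of freedom would lower these figures further.

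The point is secondary to the larger error that 120 does not follow from 1.7/4.80, which already leaves about 40% power at the plan's own effect. It is distinct because repairing that arithmetic alone would leave the independence assumption in place. It does not show that enrolment must change.

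**What to change.** When the Sample size calculation in section 2.8 is corrected, keep 120 participants and:

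1. Restate power at d = 0.354 and the difference detectable with 80% power, multiplying the variance by (1 + DE)/2, with DE = 1 + (m − 1) × ICC in the exercise arm only.
2. Show ICC 0.01, 0.05 and 0.10 for the therapist level in the written model (m about 24) and, as a sensitivity analysis, for exercise groups (m about 8 to 14).
3. State which contrast the power refers to and any baseline correlation assumed.
4. Note that two therapists leave few degrees of freedom for the clustering level.
5. Amend the adequate-power sentence in section 3.2 to match.

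The cost is a short recalculation and some rewording, with no change to enrolment, treatment or analysis. The downside is a less favourable stated power.

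### The stated inputs (difference 1.7, SD 4.80) do not give 120 participants at 80% power; on the two-group comparison that Cohen's d implies, 120 gives about 40% after dropout

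*Protocol article*

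**What the plan says.** Section 2.8 (Sample size calculation) names G*Power 3.1 and describes the effect size in two steps: "The difference between means of a meta-analysis 1.7 [26] was divided by the standard deviation" of another cited study, "4.80 to obtain Cohen’s d". The value of d is not printed. The result follows directly: "a sample size of 120 participants was calculated (60 in each group), with a statistical power of 80%, alpha of 5"%. The full list of conditions reads "with a statistical power of 80%, alpha of 5%, and 20% dropout rate".

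The paragraph does not state the test family, the sidedness, a correlation between repeated measurements, the number of measurements, or the outcome to which 1.7 and 4.80 belong. The trial has two primary outcomes: pain on a 0–10 scale and disability on the 0–24 Roland-Morris questionnaire (RMDQ).

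Section 3.2 lists the calculation among the strengths: "The sample size was calculated to provide adequate statistical power to detect intergroup differences in the primary outcome".

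**The concern.** The paragraph prints both its inputs and its answer, so a reader can check one against the other, and they do not agree. An effect of roughly a third of a standard deviation is modest, and 48 analysed participants per arm is far from enough to detect it with 80% power in a plain two-group comparison.

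At stake is how the result will be read. If the trial is believed to have 80% power for its planning effect, a non-significant difference will be taken as fairly strong evidence against the exercise programme. At about 40% power it is not. Section 3.2 reinforces the belief by presenting the power as a strength.

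**Working it through.** **Inputs, all from section 2.8:** difference 1.7; SD 4.80; power 80%; alpha 5% (sidedness not stated, so both were tried); dropout 20%; 60 per group.

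**Effect size.** d = 1.7 / 4.80 = 0.354.

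**Attempt to reproduce 120.** For two independent means, the normal approximation is n per arm = 2(z_alpha + z_power)² / d².

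- Two-sided: 2(1.960 + 0.842)² / 0.354² = 125.1, so 126. The exact noncentral-t calculation gives 127 per arm, 254 in all. With dropout: 127 / 0.8 = 158.75, so 159 per arm and **318 randomised**. Multiplying by 1.2 instead gives 306.
- One-sided: 2(1.645 + 0.842)² / 0.354² = 98.6, so 99; noncentral t gives 100 per arm. With dropout: 100 / 0.8 = 125 per arm and **250 randomised** (240 with the factor 1.2).

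Neither gives 120. Even a one-sided test with no dropout allowance needs 200. One possible origin, which is conjecture only, is that the one-sided 100 per arm times 1.2 equals 120 *per group*, and a per-group figure was taken as the total.

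**Power that 120 gives.** Noncentrality = d × √(n/2), with n analysed per arm.

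| Analysed per arm | Noncentrality | Two-sided power | One-sided power |
|---|---|---|---|
| 48 (60 less 20%) | 0.354 × √24 = 1.74 | 40% | 53% |
| 60 (no dropout) | 0.354 × √30 = 1.94 | 49% | 61% |

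**Detectable effect.** At 48 per arm, 80% two-sided power needs d = 0.578. With SD 4.80 that is 0.578 × 4.80 = 2.77 points, and 2.77 / 1.7 = 1.63, so 63% larger than the planning difference.

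**What a more efficient analysis could add.** The correlation r below is assumed; the article gives none. All figures are for 48 per arm, two-sided, d = 0.354.

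- Baseline-adjusted comparison at one follow-up: the variance is multiplied by 1 − r².
- Baseline-adjusted average over the three follow-ups, with equal correlation r between all visits (compound symmetry): the variance is multiplied by (1 + 2r)/3 − r².

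| r | Variance factor, one follow-up | Power | Variance factor, average of three | Power |
|---|---|---|---|---|
| 0.5 | 0.75 | 51% | 0.417 | 76% |
| 0.6 | 0.64 | 57% | 0.373 | 80% |
| 0.7 | 0.51 | 67% | 0.310 | 87% |

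A single follow-up reaches 80% only at r of about 0.79; the average over three follow-ups reaches it at about 0.6.

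**Repeated-measures ANOVA options.** With f = d/2 = 0.177, a within-between interaction with two measurements and correlation 0.25 needs 96 analysed, and 96 / 0.8 = 120. So one combination of settings does return the printed figure. None of those settings is stated, however, and section 2.4 plans four assessments. The effect is also not the one described: with equal baselines and a difference of d at one follow-up, the interaction effect is f = d/4 = 0.089. With that value, 80% power at 48 per arm needs a correlation of about 0.81.

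**The case against.** The strongest defence is that the planned analysis is not a t-test. Section 2.8 specifies a mixed linear model with treatment, time and their interaction, over a baseline and three follow-ups. A baseline-adjusted effect averaged over the follow-ups would reach 80% power with 96 analysed at a correlation of about 0.6, which is not far-fetched, and one repeated-measures setting in G*Power returns exactly 120. This stands as a reason not to call the trial underpowered in general. It does not rescue the paragraph, which derives a Cohen's d and presents 120 as its consequence, without a correlation, a contrast or a number of measurements.

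A second defence is that primary results will be shown as mean differences with 95% confidence intervals and read against minimal important differences (RMDQ above 5, pain above 2). If the scale is the RMDQ, the detectable 2.8 points lies below 5. This lowers the risk that a null result is misread, but the stated planning difference is 1.7, and the 80% claim is attached to that.

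Three stronger readings are tempting but not supported:

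- *A non-significant result is more likely than not if the planning effect is true.* This holds for the unadjusted two-sided comparison at one time point. With baseline adjustment, power is 51% to 67% at the correlations shown, and higher for the average.
- *Only a correlation near 0.8 could make 120 sufficient.* This holds for a single follow-up, not for an average over three.
- *The inputs are RMDQ figures.* An SD of 4.80 is close to 5, the largest possible on a 0–10 scale, so the RMDQ is likely. The article does not say so, and the cited sources are not at hand. If 1.7 and 4.80 come from different scales, d itself has no meaning.

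The lack of a separate calculation for the other primary outcome is not part of this point, since an article may leave that to the full protocol.

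**Conclusion.** The point holds. Under the two-group comparison that a Cohen's d implies, the stated inputs require about 318 randomised (two-sided) or 250 (one-sided), against 120 planned. The 80% claim in section 2.8 and the adequate-power sentence in section 3.2 are unsupported as written.

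The figure of about 40% is conditional. It assumes d = 0.354, a two-sided test, no baseline adjustment, one time point and 96 analysed. It also ignores any clustering by therapist or exercise group, which would tend to raise the requirement. The detectable 2.8 points assumes that 4.80 is the right SD on the right scale. What does not depend on the choice of analysis is that the article states nothing that takes the reader from 1.7 and 4.80 to 120 at 80% power.

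**What to change.** Keep the sample size at 120 and correct the text.

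1. In section 2.8, first name the outcome and scale of both 1.7 and 4.80, and confirm that they are the same. State the test and its sidedness.
2. Replace the 80% claim in one of two ways:
   - give the power that 120 randomised and 96 analysed provide (about 40% for d = 0.354 with a two-sided t-test) and the difference detectable with 80% power (about 2.8 points if the SD is 4.80); or
   - give the power of the planned mixed model for a named contrast, with the correlation assumed and a range around it.
3. In section 3.2, correct the sentence on adequate power to match, or delete it.

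The cost is rewording in two sections and a less favourable stated power. No extra participants are needed.

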#### Analysis of treatment effects

The statistical analysis will be performed following the intention-to-treat analysis principles [56, 57]. The blinded statistician will be given coded data, the normality will be tested using the Kolmogorov-Smirnov test and the homoscedasticity of the data will be tested using the Levene test. Then, considering normal distribution, an analysis of mixed linear models (random intercepts and fixed coefficients) will be conducted, which incorporated terms for treatment, time, and the treatment-time interactions. As two physical therapists will be responsible for implementing the GBE will be applied multilevel analyses with participants nested by physiotherapist. In this sense, level 1 being the different time points, level 2 the subject, and level 3 the physical therapists.

Mean differences and their confidence intervals (CIs) at 95% will be presented. Primary outcome results will be interpreted based on the minimal clinically important difference (MCID) estimated for the adult population (i.e., RMDQ > 5 and NRS > 2) points [58]. All statistical analyses will be performed with SPSS (IBM Corp. Released 2013. IBM SPSS Statistics for Windows, Version 22.0. Armonk, NY: IBM Corp).

In addition, the sample will be dichotomized for improvement / maintenance according to the clinically important differences. The absolute risk reduction will be obtained by subtracting the GBE group risk by the control group risk. This data will be used to calculate the number needed to treat (NNT) (100% / by reducing the absolute risk).

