### 2.4 Procedure and outcome measures

All eligible older people will receive information about the study and sign an informed consent form prior to participation. Baseline assessment (in person) will include age, sex, history of falls, duration of symptoms, prognosis rating (STarT Back Screening Tool) [33], functional capacity (Short Physical Performance Battery) [34], cognitive function (Mini Mental State Examination), and the primary and secondary outcomes. Primary and secondary outcomes will be assessed (in person) again at the end of the intervention (i.e., 8 weeks after randomization) and at the 6 and 12-months follow-up. Fig 2 represents the flow of participants during the study.

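### The mixed model names random intercepts only; if correlation between visits decays, the 12-month change-from-baseline test may run at about 6.5–9% rather than 5%

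*Protocol article*

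**What the plan says.** Section 2.8 (Analysis of treatment effects) plans "mixed linear models (random intercepts and fixed coefficients"), "which incorporated terms for treatment, time, and the treatment-time interactions". Because two therapists deliver the programme, it adds a hierarchy with "level 1 being the different time points, level 2 the subject, and level 3 the physical therapists". It names no random slope, no other residual covariance and no robust standard error. A Levene test is planned, but nothing is said to follow from it for the covariance model, and it does not address correlation between visits.

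Section 2.4 measures the primary outcomes at baseline, then "again at the end of the intervention (i.e., 8 weeks after randomization) and at the 6 and 12-months follow-up". The stated result is "Mean differences and their confidence intervals (CIs) at 95% will be presented". The text does not say whether these are differences at a visit or differences in change from baseline. It also does not say how the baseline value enters the model. No baseline covariate is named, so baseline as a fourth outcome row is the natural reading, but it is an inference.

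**The concern.** A random intercept per participant with all other coefficients fixed implies compound symmetry. The correlation between baseline and 8 weeks is then assumed equal to that between baseline and 12 months, and the variance is assumed equal at all four visits. The therapist level adds only another random intercept and does not relax this.

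The visits are unequally spaced over a year, so correlation with baseline may well fall with time. Section 2.3 also sets entry minima (RMDQ 4 or more, NRS 3 or more) that do not apply at follow-up, so the baseline SD may be smaller than later SDs. A compound-symmetric fit pools these quantities, so contrasts with different true variances receive the same model variance. The affected estimates and intervals are the trial's main result.

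**Working it through.** **Inputs from the article.** Four visits (baseline, 8 weeks, 6 months, 12 months); 60 per arm; 20% dropout; alpha 5%, taken as two-sided because the article does not say. It states no visit-specific error rate, so alpha is the only plan figure to reproduce.

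**Assumed inputs.** All correlations and relative SDs below. The therapist level is left out.

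**Formulas.** With balanced data, a random-intercept fit settles on the averaged variance and averaged covariance.
- Model variance of change = 2 × (mean variance − mean covariance).
- True variance of change from baseline to visit t = V0 + Vt − 2·C0t.
- SE ratio = √(model variance / true variance).
- Actual error = 2 × [1 − Φ(1.96 × SE ratio)].
- For the plain difference at visit t, SE ratio = √(mean variance / Vt).

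**Compound symmetry, correlation 0.5.** Model variance 2 × (1 − 0.5) = 1; true variance 2 − 2 × 0.5 = 1; ratio 1. The error is 5.0%, as planned.

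**Scenario A: correlations 0.60/0.50/0.40 by lag, equal SDs.**
- Mean correlation = (3 × 0.60 + 2 × 0.50 + 0.40)/6 = 0.533. Model variance = 2 × (1 − 0.533) = 0.933.
- 12 months: true variance 2 − 0.80 = 1.20; ratio √(0.933/1.20) = 0.88; error 8.4%.
- 8 weeks: true variance 2 − 1.20 = 0.80; ratio √(0.933/0.80) = 1.08; error 3.4%.

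**Scenario B: baseline correlations 0.40/0.35/0.30, follow-up correlations 0.65/0.55/0.65, equal SDs.**
- Mean correlation = 2.90/6 = 0.483. Model variance = 1.033.
- 12 months: true variance 1.40; ratio 0.86; error 9.2%.
- 8 weeks: true variance 1.20; ratio 0.93; error 6.9%.

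Error of the change contrast, closed form:

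| Assumed correlations | 8 weeks | 6 months | 12 months | 12 months, baseline SD 20% smaller |
|---|---|---|---|---|
| Compound symmetry 0.50 | 5.0% | 5.0% | 5.0% | 4.0% |
| Mild decay 0.55/0.50/0.45 | 4.2% | 5.4% | 6.6% | 5.4% |
| Scenario A | 3.4% | 5.8% | 8.4% | 7.0% |
| Scenario B | 6.9% | 8.1% | 9.2% | 8.0% |

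**Effect of truncation, shown for scenario A.** With relative SDs 0.8, 1, 1, 1:
- Mean variance = (0.64 + 3)/4 = 0.91.
- Mean covariance = (0.48 + 0.40 + 0.32 + 0.60 + 0.50 + 0.60)/6 = 0.483.
- Model variance = 2 × (0.91 − 0.483) = 0.853. True 12-month variance = 0.64 + 1 − 2 × 0.32 = 1.00.
- Ratio √0.853 = 0.92; error 7.0%. The smaller baseline SD lowers the inflation of this contrast.

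**Plain between-group difference at a follow-up visit.** With equal SDs the ratio is 1 and the error is 5.0% whatever the decay. With baseline SD 20% smaller, the ratio is √(0.91/1) = 0.954 and the error is 6.2%. SDs would have to rise steadily, for example 4/5/5.5/6, to reach about 9% at 12 months: mean variance (16 + 25 + 30.25 + 36)/4 = 26.81; ratio √(26.81/36) = 0.863; error 9.1%.

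**Simulation check.** Using 20,000 null trials per scenario with complete data and 60 per arm, the 12-month change test ran at 5.2% (compound symmetry), 6.8% (mild decay) and 8.6% (scenario A). With 48 per arm the figures were 4.9%, 6.5% and 8.3%. First-order autoregressive correlation by visit gave 9.3% at 0.5, 11.6% at 0.7 and 12.8% at 0.8 (60 per arm).

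**The case against.** The strongest reply is that no error has been demonstrated. The article contains no correlation and no visit-specific SD, random-intercept models are common, and under compound symmetry the planned standard errors are right. A reader might infer that the standard errors are simply wrong; the document does not support that. This part of the objection stands in full, and the point is therefore conditional.

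Second, the inflation belongs to one contrast, which the article does not name as its result. A reader might infer that every 12-month treatment estimate is tested at about 9%. With equal SDs the plain difference at a visit is tested at 5.0%. If baseline were a covariate instead of an outcome row, the 12-month error would be about 6.5% in scenario A and 5.4% in scenario B. This also stands, although the article excludes neither contrast.

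Third, a reader might take the entry minima as a further cause of the same inflation, or conclude that the 8-week interval is too wide. Neither follows. A smaller baseline SD reduces the change-contrast inflation (8.4% to 7.0%, and 9.2% to 8.0%). The 8-week error is below 5% in scenario A and above it in scenario B.

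Last, residual covariance is often left to an analysis plan, and naming a random intercept does not rule out a structured residual as well. That softens the point but does not remove it. The article does not leave the covariance open: it states a choice, and a safer one is available at almost no cost.

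**Conclusion.** The point holds in conditional form. The stated model assumes equal variances and equal correlations across visits spanning a year, and nothing in the article supports or checks the correlation assumption. If baseline is an outcome row, SDs are equal and correlation decays, the 12-month treatment-by-time contrast runs at about 6.5–9% instead of 5%. Stronger decay takes it higher, to 12.8% in the most extreme case simulated. The 8-week test may fall on either side of 5%. A baseline SD 20% smaller puts the plain difference at a follow-up visit at about 6% and brings the change-contrast figures down to about 5.4–8%. Under compound symmetry there is no problem.

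Every figure depends on assumed correlations and SDs, on complete balanced data and on leaving out the therapist level. This is a worthwhile, cheap improvement to the model, not a proven error in the planned result.

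**What to change.** Replace the participant random intercept with an unstructured residual covariance over visits. In SPSS MIXED this is a REPEATED statement on visit with COVTYPE(UN), REML and Satterthwaite degrees of freedom. Prespecify a heterogeneous Toeplitz structure as the fallback if the model does not converge. In the same sentence, say whether baseline is an outcome row or a covariate, and whether the reported mean difference is at a visit or in change from baseline.

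The cost is a few more covariance parameters: 4 × 5/2 = 10 for four visits, or 3 × 4/2 = 6 if baseline is a covariate, against two for a random intercept plus residual. Effective degrees of freedom fall slightly. The planned 120 participants can support this and no new data are needed. Compound symmetry is a special case of the unstructured form, so little is lost if it is true. That the change restores an error of about 5% is expected from theory; it was not simulated here.
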